# Study Protocol for a Multicenter, Randomized Controlled Trial to Improve Upper Extremity Hemiparesis in Chronic Stroke Patients by One-to-One Training (NEURO^®^) with Repetitive Transcranial Magnetic Stimulation

**DOI:** 10.3390/jcm11226835

**Published:** 2022-11-18

**Keywords:** occupational therapy, upper limb function, study protocol, stroke

## Abstract

During recovery from upper limb motor paralysis after stroke, it is important to (1) set the exercise difficulty level according to the motor paralysis severity, (2) provide adequate exercises, and (3) motivate the patient to achieve the goal. However, these factors have not been well-formulated. This multicenter, randomized controlled trial study aims to examine the therapeutic effects of these three factors on patients undergoing a novel intervention using repetitive transcranial magnetic stimulation and intensive one-to-one training (NEURO^®^) and to formulate a corresponding research protocol. The control group will receive conventional NEURO^®^ occupational therapy. In the intervention group, four practice plans will be selected according to the Fugl-Meyer assessment (FMA-UE) scores of the upper extremity. The goal is to predict the post-treatment outcomes based on the pre-treatment FMA-UE scores. Based on the degree of difficulty and amount of practice required, we can formulate a practice plan to promote upper limb motor recovery. This occupational therapy plan will be less influenced by the therapist’s skill, facilitating effective rehabilitation. The study findings may be utilized to promote upper limb motor paralysis recovery and provide a basis for proposing activities of daily living adapted to upper limb function.

## 1. Introduction

Approximately 80% of stroke patients develop motor paralysis [1]. Motor paralysis of the upper extremity limits patients’ activities of daily living (ADL) and reduces their quality of life [2,3]. To improve the motor function of the upper extremity in stroke patients, it is necessary to induce neuroplasticity in the patient’s brain through continuous rehabilitation [4,5,6]. Novel intervention using repetitive transcranial magnetic stimulation (rTMS) and intensive one-to-one training (NEURO^®^) is one such approach. 

The role of rTMS in NEURO^®^ is to pre-condition for rehabilitation by regulating movement-related neural activation. The effects of rTMS depend on the location, frequency, and intensity of the stimulation [7,8]. For example, in transcranial magnetic stimulation in NEURO^®^, the primary motor cortex of the patient’s intact cerebral hemisphere is irradiated at 2400 pulses per day [6]. The stimulation intensity is defined as 90% of the resting motor threshold, with the first dorsal interosseous muscle of the non-paralyzed side as the target muscle. rTMS attenuates abnormal muscle tone by decreasing the excitability of cortical and spinal anterior horn cells and modulating interhemispheric inhibition [9,10,11]. For stroke patients in the acute and convalescent (with stable symptoms 1 or 2 months after onset) phases, methods have been developed to increase neural excitability by applying high-frequency rTMS (>4 Hz) to the affected cerebral hemisphere [12,13,14]. Methods have also been developed to stimulate the bilateral cerebral hemispheres [15]. Rehabilitation in NEURO^®^ is intended to promote use-dependent plasticity of the brain by repeated motor exercises under the condition that the patient’s interhemispheric inhibition is regulated by rTMS. Occupational therapists instruct the patients on NEURO^®^ regarding the (1) functional motor exercises in the proximal and distal parts of the upper limb, (2) movement exercises including reaching and manipulating objects, (3) ADL exercises using the paralyzed side, and (4) ADL instruction and self-exercises to encourage the usage of the paralyzed side in daily life [4,5,6].

The goal of patients treated with NEURO^®^ is to reacquire ADL using the paralyzed side. In occupational therapy, compensatory movements using the non-paralyzed side, assistive devices, and assistive technology may be applied to supplement the patient’s motor function to reacquire the target activities [16,17,18]. However, in some cases, improving the motor function of the affected side may increase the possibility of patients acquiring the desired ADL. A hemiplegic patient needs at least 20 h of practice during a two-week hospitalization to recover upper limb motor function [19]. The number of stimulated upper limb movements is estimated to be 420 per session [19,20]. Rehabilitation is also more effective when patients are aware of their goals for the recovery of motor function and achievement of ADL [21,22]. Clinical occupational therapists presumably share the treatment goals with patients based on the physician’s prediction of recovery after treatment and provide selected exercises in appropriate amounts according to the characteristics of individual patients’ motor paralysis. The motor function of patients undergoing NEURO^®^ can be predicted using the Fugl-Meyer assessment of the upper extremity (FMA-UE) score [23]. NEURO^®^ reportedly improves upper limb motor function in patients regardless of the stroke type [24]. The content of rehabilitation provided by the therapist presumably affects the patient’s recovery; however, this has not been verified.

Occupational therapists intervene with the aim of helping patients acquire their target movements. They induce neuroplasticity by rTMS after considering the severity of motor paralysis. In previous studies on NEURO^®^, occupational therapy exercises were determined by the physician and therapist-in-charge with the consent of the patient, and 40 to 60 min of treatment were provided twice a day [4,5,6]. However, when compared with the well-established stimulation method of rTMS, the difficulty level, amount of practice, and goal settings in NEURO^®^ are not yet formalized and are dependent on the discretion of the physicians and therapists. Motor paralysis and related disability in daily life are highly individualized; while it is difficult for patients to have an idea of the training and recovery needed, this is not a problem for therapists with sufficient clinical experience. The issues faced include: (1) unclear criteria for selecting upper limb motor exercises based on the severity of motor paralysis, (2) unavailability of guidelines for the number of upper limb exercises to be performed by patients, and (3) unclear goal-sharing between patients and therapists regarding the recovery of upper limb motor function and the use of upper limbs in ADL. Therefore, a formalized occupational therapy in NEURO^®^ will uniformize the treatment method and stabilize the functional recovery of patients.

This study aims to evaluate the therapeutic effect of NEURO^®^ on patients by providing a certain amount of selected functional exercises based on the severity of the patients’ motor paralysis. We also define a research protocol in this study. It is hypothesized that the occupational therapy intervention used in this study will improve the patients’ upper limb motor function compared to the conventional intervention method used for patients who receive NEURO^®^. We believe that if the treatment plan for NEURO^®^ occupational therapy is established according to the characteristics of the patients’ motor paralysis, the patients will be less influenced by the skills and years of experience of the assigned occupational therapist, and the effectiveness of rehabilitation will be more stable than that of conventional occupational therapy. This stability will contribute to the improvement of the patient’s goal for ADL.

## 2. Materials and Methods

### 2.1. Aims

The purpose of this study is to evaluate the therapeutic effect of NEURO^®^ on patients by providing a certain amount of selected functional exercises based on the severity of the patients’ motor paralysis. We also aim to define a research protocol in this study.

### 2.2. Study Design

We will use a multicenter, randomized controlled trial design to conduct this study.

### 2.3. Participants and Settings

The study participants are patients with a history of stroke who are admitted to a NEURO^®^-certified facility and have undergone NEURO^®^. NEURO^®^ is performed in 14 registered NEURO^®^-accredited facilities by trained staff who have passed the examination of the Department of Rehabilitation Medicine, The Jikei University School of Medicine [25]. The inclusion criteria for patients, based on the rTMS guidelines, are as follows: (1) hemiplegia after first stroke, (2) age ≥ 20 years, (3) 6 months after stroke onset, and (4) no bilateral cerebrovascular disease [26]. Exclusion criteria are as follows: (1) patients with a diagnosis of dementia based on a Mini Mental State Examination score below the cutoff point, (2) patients with physical or psychiatric diseases requiring medical management, (3) patients with seizures within 1 year, (4) patients with intracranial clips or cardiac pacemakers, (5) patients with a history of subarachnoid hemorrhage, and (6) patients with fever (≥37 °C), upper respiratory tract inflammation, malaise, and taste or olfactory symptoms when seen by a rehabilitation physician affiliated with a NEURO^®^ -accredited facility prior to admission.

### 2.4. Participant Characteristics

Participant characteristics such as age, sex, height, weight, body mass index (BMI), and dominant hand will be investigated. Medical information regarding the type of disease (cerebral infarction, cerebral hemorrhage, etc.), paralyzed side, post-onset period, and the years of clinical practice of the treating therapists will be investigated (Table 1).

### 2.5. Sample Size

The sample size was estimated via a priori analysis using G*Power. We selected goodness-of-fit (F test) and analysis of covariance (ANCOVA) (for fixed effects, main effects, and interactions) for finding the sample fitness and size. The other data were set as α = 0.05, 1 − β (power) = 0.8, numerator df = 1, number of groups = 4, and number of covariates = 4. Based on this calculation, the minimum sample size was estimated to be 128 (64 in each group). Since the subjects were hemiplegic patients, the minimum sample size was defined as 128 subjects (64 subjects in each group).

### 2.6. Randomization

A random number table, created using Microsoft Excel (Microsoft, Redmond, WA, USA), will be used for the allocation of patients into the intervention and control groups. The random number table is created at each hospital and maintained by the allocation manager at each hospital.

### 2.7. Sequence Generation

Simple randomization will be used for allocation. Once patients who meet the eligibility criteria are enrolled, they will be assigned using a random number table generated at each hospital.

### 2.8. Allocation Concealment Mechanism

Allocation will be performed by random assignment using a table of random numbers created at each hospital. The order of patient allocation will not be concealed from the person in charge of allocation. Patients will be assigned in the order in which they are registered according to the random number table (Figure 1).

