### 2.14. Statistical Analysis

A multivariate ANCOVA will be conducted to test the hypothesis that the occupational therapy intervention in this study will improve motor function in chronic stroke patients undergoing NEURO^®^ when compared with conventional occupational therapy interventions. The dependent variable will be the date or period of assessment, and the independent variables will be the change in scores of the primary assessment (FMA-UE) and the secondary assessments (ARAT and JASMID). The covariates are age, sex, BMI, and time since onset. JAMOVI version 2.2.1 (JAMOVI Project, Sydney, Australia) will be used for statistical analysis.

The primary analysis will be conducted when the intervention and control group samples reach a total of 64 cases each in all settings. The secondary analysis will be conducted when the number of patients in each group exceeds 60% of all participating centers (Figure 6).

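### Each hospital makes and holds its own random list with the order visible to its local allocator, so the next arm can be known on site before a patient is registered; the enrolment needed for 64 per arm is also unstated.

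*Protocol article*

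**What the plan says.** All references are to the protocol article.

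- **Who makes and holds the list (section 2.6, Randomization).** "The random number table is created at each hospital and maintained by the allocation manager at each hospital". The tool is Microsoft Excel. Section 2.12 and the caption of Figure 6 give 14 facilities.
- **Type of list (section 2.7, Sequence Generation).** "Simple randomization will be used for allocation". No blocks or strata are described.
- **Concealment (section 2.8, Allocation Concealment Mechanism).** "The order of patient allocation will not be concealed from the person in charge of allocation". The section continues: "Patients will be assigned in the order in which they are registered according to the random number table".
- **Who is open (section 2.9, Blinding).** Physicians, occupational therapists and the evaluator all know the assignment. Patients and the data analyst are to be kept unaware.
- **Size and trigger.** Section 2.5 (Sample Size) sets 128 patients, 64 per group, as a minimum. Section 2.14 (Statistical Analysis) says: "The primary analysis will be conducted when the intervention and control group samples reach a total of 64 cases each in all settings".
- **Covariates (section 2.14).** Age, sex, BMI and time since onset.

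**The concern.** Concealment protects the step between finding an eligible patient and registering that patient. Whoever decides at that step must not know the next assignment. Here the section headed as the concealment mechanism says that the person running allocation does know it. That person sits in the recruiting hospital, and the next registered patient simply takes the next entry.

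The setting leaves room for such knowledge to act. These are planned two-week admissions of patients at least six months after stroke, so the date of registration can move. Some exclusion criteria in section 2.3 call for judgement, for example a physical or psychiatric disease that needs medical management. A patient thought likely to do well could be registered now or held back, depending on the next arm.

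The analysis would not repair this. Section 2.12 uses the admission FMA-UE to predict recovery, so the plan itself treats baseline severity as prognostic. Yet section 2.14 lists neither that score nor hospital as a covariate. Analysing change scores subtracts the baseline, but it does not remove a dependence of recovery on severity.

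A lesser question is how simple randomisation fits an analysis that waits for 64 cases in each arm.

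**Working it through.** **1. Foreknowledge: reading the sections together**

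- Section 2.6: the list is local and kept by a local manager.
- Section 2.8: its order is visible to the person in charge of allocation, and entries are used in order of registration.
- It follows that the holder knows the arm of the next patient before that patient is registered. This needs no assumption.
- Simple randomisation is not itself guessable. The weakness is access to the list.

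The bias cannot be sized from the document. As a form only: suppose a share q of registrations is steered, so that the arms differ by δ points in expected FMA-UE change among the steered patients. The bias in the group difference is then about q × δ. Sample size does not enter.

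**2. The plan's own sample size**

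- Inputs (section 2.5): "α = 0.05, 1 − β (power) = 0.8, numerator df = 1, number of groups = 4, and number of covariates = 4".
- The effect size is not stated. Assumption: Cohen's f = 0.25.
- Noncentral F with λ = N × f², df1 = 1, df2 = N − 4 − 4.
- N = 128: λ = 128 × 0.0625 = 8, df2 = 120, power 0.801. N = 127 gives 0.798.
- So 128 is reproduced at f = 0.25. At f = 0.20 the answer would be 199, and at f = 0.30 it would be 90.

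**3. Split of the arms at exactly 128**

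A 1:1 ratio is inferred from 64 and 64. Arm size X ~ Binomial(128, 0.5).

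- SD = √128 / 2 = 5.7; central 95% range 53 to 75.
- P(X = 64) = 0.0704.

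Power uses λ = d² × n1 × n2 / 128 with d = 2f = 0.5:

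| Split | λ | Power |
|---|---|---|
| 64:64 | 0.25 × 4096 / 128 = 8.00 | 0.801 |
| 58:70 | 0.25 × 4060 / 128 = 7.93 | 0.798 |
| 53:75 | 0.25 × 3975 / 128 = 7.76 | 0.789 |

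Averaged over all splits, power is 0.798. The loss is about 0.3 percentage points.

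**4. Enrolment until both arms hold 64**

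Let T be the total when the smaller arm reaches 64. Then P(T ≤ t) = P(64 ≤ X ≤ t − 64), with X ~ Binomial(t, 0.5).

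- Mean 137.0, median 135, 90th percentile 147, 95th percentile 152.
- Check by hand: at 128 the smaller arm is short by |X − 64|, with mean 64 × 0.0704 = 4.5. Each missing patient takes two further allocations on average, so the mean is 128 + 2 × 4.5 = 137.
- 137 / 128 = 1.07, about 7% above the stated minimum.
- These counts assume that every randomised patient becomes a case; dropout would add to them.

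**5. Effect of hospital-stratified blocks on balance**

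Illustration with blocks of 4 and each hospital stopping at a random point in a block. The variance of arm size per hospital is (0 + 1/4 + 1/3 + 1/4) / 4 = 0.208. Over 14 hospitals it is 2.92, so the SD is 1.7, against 5.7 under simple randomisation.

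**The case against.** Several stronger readings are tempting, and the document does not support them.

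- **That treating staff can foresee the next arm.** Section 2.8 states foreknowledge only for the person in charge of allocation. Being open to assignment under section 2.9 is not the same as seeing the list beforehand. A separation of roles may stand in the full protocol, which a condensed article need not repeat. This stands as a limit on the claim. It does not remove the point, because local custody and a visible order are stated rules, and nothing shown keeps the holder apart from recruitment.
- **That simple randomisation is incompatible with 64 per arm.** It is not. The 128 is a minimum, the analysis waits for both arms, and a rule based on arm counts does not look at outcomes. The 7% chance of an exact 64:64 split matters only if recruitment stops at 128, which no section says. What remains is that the expected total is unstated.
- **That a full arm would be closed, making about the last 9 allocations (90th percentile 18) certain.** No section closes an arm. It is only a reason to say explicitly that none will be.
- **That lopsided hospitals confound the comparison or cost about 11% of information.** With 9 patients per hospital (128 / 14, equal recruitment assumed), a split of 7:2 or worse has probability 2 × (1 + 9 + 36) / 512 = 0.18. Such chance imbalance is random error, not systematic bias. The 11% applies only to an analysis conditioned on hospital, which section 2.14 does not plan.

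It is also true that blocks are easier to guess for open staff than simple randomisation. That is a real cost of the preferred remedy.

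**Conclusion.** The concern holds in limited form. The document states an arrangement under which the next arm is known on site to the list holder before registration, with no stated barrier between that person and enrolment, treatment or evaluation. Selective enrolment is therefore possible. It is not shown to be likely, and its size cannot be derived from the document. A larger sample would not cure it, and the listed covariates leave out both hospital and admission FMA-UE. This is worth correcting before the first patient.

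The arm-size matter is secondary. Under 1:1 simple randomisation the plan implies about 137 patients on average (90th percentile 147) without saying so. Power is practically unaffected by imbalance at 128, given the assumed f = 0.25.

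**What to change.** Replace the 14 local lists with one centrally generated and held allocation.

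- The holder should be an existing person who does not enrol, treat or evaluate at any site. Being based at a lead institution is not enough if that institution also recruits and the person takes part there.
- Release one assignment at a time, only after consent, eligibility and the admission FMA-UE have been logged.
- Preferably stratify by hospital, with block sizes varied at random and not disclosed. The arms then come close to equal near 128, though not exactly equal (SD of arm size about 1.7 in the blocks-of-4 illustration).
- Keep the floor of 64 cases per arm as the trigger. A trigger at 128 randomised would lose that floor as soon as anyone drops out.
- State the expected total enrolment, and state that neither arm is closed early. If simple randomisation is retained, the total to plan for is about 137 on average and 147 at the 90th percentile, before dropout.
- Rewrite sections 2.6 to 2.8 accordingly.

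The cost is a short amendment and one call or e-mail per patient. The drawback is that blocks are slightly more predictable to open staff than simple randomisation; varied, undisclosed sizes and central holding limit this. The required sample size does not change.

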### 2.9. Blinding

This study will be double-blind. (1) Patients who meet eligibility criteria and are enrolled will be blinded to the treatment received and to the group to which they are assigned. Physicians and occupational therapists will not be blinded to the group assignment. The evaluator is not blinded. (2) The data will be analyzed by an analyst using a dataset that has been processed in such a way that the group assignment is unknown. In order to confirm the success or failure of the patients’ blinding, therapists will ask patients which treatment they thought they received after completing NEURO^®^ treatment and then confirm whether it was the treatment actually performed.

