The minimum number of functional exercises in the intervention group will be 500 per day. The protocol of the intervention group meets the requirements of the amount and duration of exercises reported in previous studies. This study is planned in 14 NEURO^®^-certified facilities in Japan: The Jikei University Hospital, The Jikei University Daisan Hospital, Tokyo General Hospital, Nishi-Hiroshima Rehabilitation Hospital, Kimura Hospital, Kyoto Ohara Memorial Hospital, Izumi Memorial Hospital, Hakodate Shintoshi Hospital, Aomori Shintoshi Hospital, Hattanmaru Rehabilitation Hospital, Atsuchi Rehabilitation Hospital, Ainomiyako Neurosurgery Hospital, Shinagawa Rehabilitation Hospital, and International University of Health and Welfare Ichikawa Hospital. A total of 15 professionals with at least five years of experience in NEURO^®^ rehabilitation were selected as therapists. The level of difficulty of functional exercises in the occupational therapy intervention used in this study was discussed with them and decided upon via consensus. In the past, the treatment and evaluation of patients undergoing NEURO^®^ have been performed by occupational therapists who have completed the prescribed training at NEURO^®^-accredited facilities. The treatment and evaluation procedures for the intervention group will be fully explained to the occupational therapists by at least one expert selected at each site who has discussed this study protocol with the occupational therapists. The expert at each site will supervise the occupational therapists to ensure that they fully understand and implement the study protocol for the intervention group.

The treatment goal is set according to the study by Hamaguchi et al. [23], and the predicted value of recovery of upper limb motor function by NEURO^®^ is calculated using the FMA-UE score obtained on the first day of hospitalization [23]. The physician-in-charge will explain to the patients the predicted score at discharge, the target ADL, and the plan of functional exercises to be performed to achieve the goal. They also promote the patient’s understanding of these plans. These procedures are performed by the physician and occupational therapist within two days of admission.

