## Figures and Tables

**Figure 1 jcm-11-06835-f001:**
[figure not shown]
Schedule of enrollment, interventions, and assessments. FMA-UE, Fugl-Meyer assessment of the upper extremity; ARAT, Action Research Arm Test; JASMID, Jikei Assessment Scale for Motor Impairment in Daily Living. Investigators will obtain informed consent from patients who meet the eligibility criteria. Patient allocation will be performed by random assignment using a table of random numbers created at each hospital. Participant characteristics and medical information will be investigated. The control and intervention groups will receive treatment for two weeks. Patients will be evaluated on the day of admission and on the day of discharge.

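### The trial is called double-blind, but the evaluator of its rater-judged primary outcome (FMA-UE) knows the arm; only patients and the data analyst are masked

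*Protocol article*

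**What the plan says.** All references are to the protocol article.

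- **Label (2.9):** "This study will be double-blind".
- **Who is masked (2.9):** patients, who "will be blinded to the treatment received and to the group to which they are assigned", and the analyst, who works on a dataset with the group hidden.
- **Who is not masked (2.9):** "Physicians and occupational therapists will not be blinded to the group assignment. The evaluator is not blinded".
- **Outcomes (2.13):** FMA-UE is primary, with a maximum of 66 and each item on a 3-point ordinal scale. ARAT is secondary, with a maximum of 57 and each item on a 4-point ordinal scale.
- **Timing (Figure 1 caption):** "Patients will be evaluated on the day of admission and on the day of discharge".
- **Target score (2.12, intervention group):** a predicted FMA-UE is calculated from the first-day score. "The physician-in-charge will explain to the patients the predicted score at discharge, the target ADL, and the plan of functional exercises". "These procedures are performed by the physician and occupational therapist within two days of admission". Section 2.11, on the control group, specifies no predicted score.
- **Covariates (2.14):** age, sex, BMI and time since onset.

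**The concern.** Readers take double-blind to mean that whoever scores the outcome does not know the arm. Here that person does, and the primary outcome depends on that person's judgement item by item. A difference in how strictly the two arms are scored cannot be told apart from a treatment effect. Masking the analyst comes too late, because the scores already exist. None of the four covariates carries information about the rater.

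The goal-setting procedure adds a second route. In one arm only, staff are told to put a number on the primary outcome scale before that scale is scored again at discharge. If the discharge rater knows the number, it can act as an anchor.

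At stake are the interpretation of the primary comparison and the weight readers give it: a positive result reported under this label would look better protected than it is.

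**Working it through.** **1. The label against the masking described in 2.9**

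| Role | Masked? |
|---|---|
| Patient | Yes |
| Physician | No |
| Occupational therapist | No |
| Outcome evaluator | No |
| Data analyst | Yes |

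Two parties are masked. The one who produces the primary data is not among them.

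**2. Does the rater know the target?** Section 2.12 has the physician and occupational therapist carry out the goal-setting steps in the intervention group. It also says that occupational therapists have in the past both treated and evaluated NEURO patients, and that treatment and evaluation procedures for this group will be explained to the occupational therapists. This suggests, without stating, that a treating therapist may score the discharge FMA-UE. Knowledge of the arm is stated outright; knowledge of the target is an inference.

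**3. The plan's own figure.** Section 2.5 gives α = 0.05, power 0.8, numerator df = 1, 4 groups, 4 covariates and N = 128. It gives no effect size. For an ANCOVA F test:

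- λ = N·f², df1 = 1, df2 = N − 4 − 4
- with assumed f = 0.25 (d = 2f = 0.5) and N = 128: λ = 128 × 0.0625 = 8, df2 = 120, power 0.801
- N = 127 gives 0.798, so 128 is the smallest adequate size

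Other assumed values give other sizes (f = 0.20 gives 199; f = 0.30 gives 90). N = 128 therefore fits f = 0.25, but the article does not state that value.

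**4. Sensitivity to a scoring shift.** Suppose there is no true effect and a mean scoring difference of b points between arms. With SD σ of FMA-UE change:

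- f = b/(2σ), λ = 128·f², df2 = 120, critical F = 3.920
- P(significant) = P(noncentral F > 3.920)

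With b = 1 and σ from 3 to 6 (all assumed):

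| σ | f | λ | P(significant) |
|---|---|---|---|
| 3 | 0.167 | 3.556 | 46.4% |
| 4 | 0.125 | 2.000 | 28.9% |
| 5 | 0.100 | 1.280 | 20.2% |
| 6 | 0.083 | 0.889 | 15.5% |

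The nominal rate is 5%. A total of 66 with items scored 0 to 2 implies 66/2 = 33 items. A 1-point mean shift therefore equals one of 33 items rated one step differently, on average, in every patient of one arm.

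At half that shift (b = 0.5) the figures are 15.5% for σ = 3 and 7.5% for σ = 6. The answer depends strongly on b, about which the article says nothing.

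**The case against.** **The open evaluator is disclosed.** Section 2.9 numbers its two masked parties and says in the same paragraph that the evaluator is not masked. This stands: the label misleads rather than conceals. Disclosure does not protect the scores, however.

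**The target need not favour the intervention.** A reader might infer that scoring towards the predicted value creates or inflates the effect. The article does not support that. Section 2.12 describes the prediction as one of recovery by NEURO, which both arms receive, and the Introduction says goal setting and amount of practice in NEURO are not yet formalized. The predicted value may therefore sit near what conventional care achieves. Scoring towards it could raise or lower intervention ratings and could even hide a true benefit. This stands, and no direction is claimed for this route.

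**Nothing says the rater knows the target.** This also stands. The text on who evaluates describes past practice. The Introduction adds that therapists presumably share goals based on the physician's prediction, so informal targets for controls cannot be excluded, although no predicted score is specified for them.

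**The numbers rest on assumptions.** Correct. The effect size, the SD and the 1-point shift are not in the article.

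**Other outcomes depend less on the rater.** JASMID is patient-reported and the WMFT is partly timed (2.13). They can support interpretation but do not protect the primary outcome, and 2.14 does not list the WMFT among the analysed scores.

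**Conclusion.** The concern holds in a limited form. The double-blind label claims a protection that the primary outcome does not have. Because FMA-UE and ARAT are judged by a rater who knows the arm, they are open to detection bias that no planned step in the analysis can remove. This follows from the text of 2.9, 2.13 and 2.14 without any assumption.

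The intervention-only predicted score is a further, conditional risk: it matters if the discharge rater knows it, and its direction is not established.

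The figures of 15.5% to 46.4% against 5% hold only for a 1-point shift, an SD of 3 to 6 points, 64 per arm and no true effect. They show how sensitive a trial of this size is to small scoring differences and do not estimate the error rate of this trial. A reader might also take 0.5 SD as the planned effect; it is only a value that reproduces N = 128.

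**What to change.** 1. **Section 2.9:** replace 'double-blind' with 'patients and data analyst masked; physicians, therapists and outcome evaluator not masked', adjusted if step 3 is adopted, and limit the conclusions accordingly.
2. **Sections 2.12 and 2.13:** state that the discharge rater is not given the predicted score or the plan number.
3. **Section 2.13:** where existing rosters allow, have discharge FMA-UE and ARAT scored in both arms by a NEURO-trained therapist already on staff who does not treat the patient and is not told the arm or target. Record for each rating whether it was masked or open, and report as open-assessed only those that were.

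**Cost:** a change of wording, an instruction to raters and some rostering effort. No visit is added and N = 128 is unaffected. The article gives no staffing figures, so some of the 14 facilities may be unable to make the swap. Masking within one site may also be imperfect, since 2.12 has an expert at each site supervising delivery of the intervention. Recording the masking status shows how far the step succeeded.
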